## Abstract

**Background:**

There are no specific generally accepted therapies for the coronavirus disease 2019 (COVID-19). The full spectrum of COVID-19 ranges from asymptomatic disease to mild respiratory tract illness to severe pneumonia, acute respiratory distress syndrome (ARDS), multisystem organ failure, and death. The efficacy of corticosteroids in viral ARDS remains unknown. We postulated that adjunctive treatment of established ARDS caused by COVID-19 with intravenous dexamethasone might change the pulmonary and systemic inflammatory response and thereby reduce morbidity, leading to a decrease in duration of mechanical ventilation and in mortality.

**Methods/design:**

This is a multicenter, randomized, controlled, parallel, open-label, superiority trial testing dexamethasone in 200 mechanically ventilated adult patients with established moderate-to-severe ARDS caused by confirmed SARS-CoV-2 infection. Established ARDS is defined as maintaining a PaO_2_/FiO_2_ ≤ 200 mmHg on PEEP ≥ 10 cmH_2_O and FiO_2_ ≥ 0.5 after 12 ± 3 h of routine intensive care. Eligible patients will be randomly assigned to receive either dexamethasone plus standard intensive care or standard intensive care alone. Patients in the dexamethasone group will receive an intravenous dose of 20 mg once daily from day 1 to day 5, followed by 10 mg once daily from day 6 to day 10. The primary outcome is 60-day mortality. The secondary outcome is the number of ventilator-free days, defined as days alive and free from mechanical ventilation at day 28 after randomization. All analyses will be done according to the intention-to-treat principle.

**Discussion:**

This study will assess the role of dexamethasone in patients with established moderate-to-severe ARDS caused by SARS-CoV-2.

**Trial registration:**

ClinicalTrials.gov NCT04325061. Registered on 25 March 2020 as DEXA-COVID19.

## Background

The acute respiratory distress syndrome (ARDS) is a catastrophic illness of multifactorial etiology characterized by diffuse, severe inflammation of the lung leading to acute hypoxemic respiratory failure requiring mechanical ventilation (MV) [1]. There is a strong association between dysregulated systemic and pulmonary inflammation and progression or delayed resolution of ARDS [2]. Glucocorticoid receptor-mediated downregulation of systemic and pulmonary inflammation is essential to accelerate disease resolution and restore tissue homeostasis and can be enhanced with glucocorticoid treatment [3].

The coronavirus disease 2019 (COVID-19) pandemic has rapidly saturated intensive care units (ICUs). Severe pneumonia is the main condition leading to ARDS requiring weeks of MV with high mortality (40–60%) in COVID-19 patients. There is no specific therapy for COVID-19, although patients are receiving drugs that are already approved for treating other diseases [4]. There has been great interest in the role of corticosteroids to attenuate the pulmonary and systemic damage in ARDS patients because of their potent anti-inflammatory and antifibrotic properties [5]. However, the efficacy of corticosteroids in viral ARDS remains controversial [6, 7], and its role in COVID-19 is unknown.

[name] et al. [8] recently published a clinical trial enrolling 277 patients with established moderate-to-severe ARDS who received either low-to-moderate doses of dexamethasone for 10 days or usual care [8]. The study demonstrated that corticosteroid therapy is associated with a sizable reduction in duration of MV and hospital mortality, in accordance with a previous meta-analysis [3]. The dysregulated inflammation and coagulation observed in COVID-19 [9] is similar to multifactorial ARDS and thus may be amenable to corticosteroid treatment to downregulate inflammation-fibroproliferation and accelerate disease resolution [2, 10]. In a recent report in 84 COVID-19 patients with ARDS from a single center in Wuhan, China, the administration of corticosteroids appeared to reduce risk of death, but this study was a non-randomized retrospective analysis [4].

What likely kills COVID-19 patients is the dysregulated systemic inflammation. We postulate that treatment with dexamethasone in the early phase of established moderate-to-severe ARDS caused by SARS-CoV-2 changes the pulmonary and systemic inflammatory response and thereby reduces mortality. If the trial is positive, it could have a large impact on patients with COVID-19 since the drug is cheap and widely available.

## Methods/design

### Justification of the study

Currently, there are no specific pharmacological therapies for COVID-19. There has been great interest in the role of corticosteroids to attenuate the pulmonary and systemic damage in patients with the acute respiratory distress syndrome (ARDS) because of their potent anti-inflammatory and antifibrotic properties [5]. Corticosteroids have been off-patent for greater than 20 years; they are cheap and globally equitable. Dexamethasone has potent anti-inflammatory effects and weak mineralocorticoid effects compared with other corticosteroids [11]. It is 20 to 30 times more potent than the naturally occurring hormone, cortisol, and four to five times more potent than prednisone [5]. In addition, dexamethasone has a long-lasting effect, allowing for a once-a-day regimen [11].

We justify the need of this study based on the positive results of a recent clinical trial, showing that dexamethasone for 10 days was able to reduce the duration of MV (between-group difference 5 days, 95% CI 2–8 days) and 60-day hospital mortality (between-group difference 15%, 95% CI 5–26%) in patients with ARDS from multiple causes [8], and on preliminary retrospective data demonstrating a decrease in mortality [4]. Our goal in this study is to examine the effects of dexamethasone on mortality and on ventilator-free days (VFDs) in patients with moderate-to-severe ARDS due to confirmed COVID-19 who still meet ARDS criteria at 12 h after ARDS diagnosis despite routine intensive management.

### Study design

The DEXA-COVID19 study is a multicenter, randomized, controlled, open-label trial involving 200 mechanically ventilated adult patients with ARDS caused by confirmed SARS-CoV-2 infection and admitted into a network of ICUs in teaching hospitals across Spain, and possibly more widely. Patients will be randomized and enrolled in Spain, and data will be collected in Spain and analyzed in Spain and Canada. Study sites are listed in Appendix 1.

The trial was designed in accordance with the Declaration of Helsinki [12], the Convention of the European Council related to human rights and biomedicine, and within the requirements established by Spanish legislation in the field of biomedical research, the protection of personal data, and bioethics, which was registered on 25 March 2020 at http://www.clinicaltrials.gov with identification no. NCT 04325061. The study protocol (Version 1, 27 March 2020) was approved by the referral Ethics Committee (Hospital Universitario La Paz, Madrid, Spain) and the institutional review boards of all participating hospitals (Additional file 1). The trial was approved by the Spanish Agency of Drugs and Medical Devices (Agencia Española del Medicamento y Productos Sanitarios) as a clinical randomized study with drugs on 30 March 2020. For inclusion into the study, approval on a written informed consent will be requested by the local investigators from the patients’ relatives or legal representatives (Additional file 2). Our protocol followed the SPIRIT (Standard Protocol Items: Recommendations for Interventional Trials) guidelines [13]. See Additional file 3 for the SPIRIT checklist of the study protocol.

### Study population

To be eligible for inclusion into this study (day 0), each patient (male or female) must fulfill the following inclusion criteria during screening and prior to enrollment: age ≥ 18 years, have a positive reverse-transcriptase-polymerase-chain-reaction (RT-PCR) assay for SARS-CoV-2 in a respiratory tract sample, be intubated and mechanically ventilated, and have acute onset of moderate-to-severe ARDS, as defined by Berlin criteria [14], which includes (i) having pneumonia, (ii) bilateral pulmonary infiltrates on chest imaging (x-ray or CT scan), (iii) absence of left atrial hypertension or no clinical signs of left heart failure, and (iv) hypoxemia, as defined by a PaO_2_/FiO_2_ ratio of ≤ 200 mmHg on positive end-expiratory pressure (PEEP) of ≥ 5 cmH_2_O, regardless of FiO_2_. Patients will be excluded from study participation if any of the following are present: routine treatment with corticosteroids during the previous week (irrespective of dose), having a known contraindication to corticosteroids, a decision by a physician stating that involvement in the trial is not in the patient’s best interest, pregnancy and breast-feeding, or participation in another trial.

### Enrollment into the study

Onset of ARDS is defined as the day and time when the patient first met moderate-to-severe ARDS criteria [14]. An enrichment strategy to decrease heterogeneity and to restrict enrollment to screened patients at higher risk of death, thereby allowing the use of mortality as a primary outcome, is used as follows. We will identify patients with established moderate-to-severe ARDS by a two-step process: (i) mandatory standardization of measurements of PaO_2_/FiO_2_ at 12 ± 3 h after the ARDS diagnosis using a standardized ventilatory setting [8, 15], on PEEP of ≥ 10 cmH_2_O and FiO_2_ of ≥ 0.5 because the cutoff value of PaO_2_/FiO_2_ is an important determinant for ARDS stratification, and oxygenation in COVID-19 pneumonia/ARDS improves in many patients after initial inclusion criteria with low-tidal volume MV, moderate to high levels of PEEP, and prone positioning [10]; (ii) only patients with a PaO_2_/FiO_2_ of ≤ 200 mmHg under these ventilatory settings are eligible for randomization.

### Randomization and masking

Eligible, consented patients will be randomly assigned in a 1:1 ratio to receive either dexamethasone plus standard intensive care or standard intensive care alone (control group). Dexamethasone will be freely provided by the health authorities in participating hospitals. Because of the emergency nature of the trial, a placebo will not be used. According to the ethical principles for medical research of the Declaration of Helsinki [12], the use of no placebo (no intervention) is acceptable when no proven intervention exists. The Spanish Agency of Drugs and Medical Devices and the Ethics Committees did not mandate a blinded design or the administration of a placebo. Central randomization will be done within the REDCap system. Local investigators in participating ICUs are the only authorized personnel to interact with the web-response system through a username and password. Once eligibility is confirmed in the eCRF, the next available treatment group is assigned by the system according to a randomization schedule prepared by a statistician and uploaded as a look-up table to the REDCap system. The computer-generated randomization schedule will use random permuted blocks of varying sizes to further ensure allocation concealment and is unavailable to those who enroll patients or assign interventions.

### Dexamethasone therapy and general procedures

Patients assigned to the dexamethasone group will receive the first dose immediately after being randomized. Patients in the dexamethasone group will receive an intravenous dose of 20 mg once daily from day 1 to day 5, and 10 mg once daily from day 6 to day 10. We selected the same doses as reported in the only published trial with dexamethasone in ARDS patients [8]. Treatment with dexamethasone will be given for a maximum of 10 days after randomization, independently of the intubation status (Fig. 1). Criteria for discontinuing intervention (exiting the trial) for a given trial participant are contemplated in the informed consent from (at patient’s legal representative request). In addition, as a request by the patient’s legal representative, allocated intervention (daily dose of intravenous dexamethasone) could be modified in case of a profound worsening of disease status (request to do-not-resuscitate orders, withdrawal of treatment and life support measures).

**Fig. 1 Fig1:**
[figure not shown]
Study design diagram

Although initially, the local investigator will assign the patient to the interventions, staff physicians and nurses will be involved in the management and treatment of enrolled patients until ICU discharge, respecting the treatment assignment during the study period. In both groups, standard intensive care will not be strictly controlled. However, in both treatment groups, physicians are asked to follow recommendations for standard intensive care management, including vasopressor support and antibiotic therapy, aimed at maintaining optimal conditions. For ventilatory management, clinicians should follow recommendations for lung-protective MV in both treatment groups: tidal volume of 4–8 ml/kg predicted body weight, plateau pressure < 30 cmH_2_O, respiratory rate to maintain PaCO_2_ between 35 and 50 mmHg, and with PEEP and FiO_2_ combinations according to the PEEP-FiO_2_ table of the ARDSnet protocol [16], ensuring that among the PEEP and FiO_2_ combinations, clinicians should use the PEEP levels that allow the reduction of FiO_2_ to the lowest level for maintaining a PaO_2_ of 60 to 100 mmHg or an SpO_2_ of 90–98% [17]. Neuromuscular blocking agents, sedation, prone positioning, and recruitment maneuvers are allowed at the discretion of the attending physician. Weaning from MV will start when the attending physician considers it clinically appropriate. In both groups, patients should be assessed daily for readiness to wean using a spontaneous breathing trial based on the ARDSnet protocol [16]. If the patient passes the trial, a decision for extubation is taken, unless there is a specific reason not to extubate. The use of drugs that are approved for treating other diseases, such as antivirals, interferon, chloroquine, or other medications, is allowed in both groups at the discretion of attending physician.

### Clinical and laboratory monitoring

All participating patients, regardless of the study arm into which they are randomized, will be monitored and managed following general standard of care practices. Patients will be assessed once daily by trained physicians and nurses using a simplified standardized case report form (CRF) that captures data on lung mechanics, gas-exchange, and routine biochemistry and hematological test on days 0 (at ARDS diagnosis), 1, 3, 6, and 10, and every 10 days, including the last day of MV, if the patient is still in the ICU (Fig. 2). The model of CRF can be obtained from the primary investigator. Recommended lab determinations include creatine phosphokinase (CPK), D-dimer, ferritin, lactate dehydrogenase (LDH), troponin, lactate, creatinine, procalcitonin, C-reactive protein (CRP), lymphocyte count, and interleukin-6 (IL-6). Viral serology (antibodies) and routine blood cultures will be indicated at the discretion of the attending physician. We will record complications, such as other infections, barotrauma, and sepsis; Acute Physiology and Chronic Health Evaluation II (APACHE II) score [18] on days 0 and 1; and the Sequential Organ Failure Assessment (SOFA) score [19], on days 0, 1, 3, 6, and the last day of MV, if the patient is still in the ICU. Serial oropharyngeal swab samples will be obtained on day 1 (before the administration of the first dose of dexamethasone) and (if possible) on days 6, 10, 14, 21, and 28 until discharge or death occurs, and tested at participating hospitals using real-time RT-PCR. RNA will be extracted using standard measures by trained personnel from the Microbiology Departments in each hospital. Sampling should not stop if a swab at a given time is negative. We will also monitor duration of MV and ICU and hospital mortality. Patients will be followed up to 60 days after randomization. Data recorded on CRFs will be double-entered into an electronic database and validated by trial staff.

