### Outcome measures

The primary outcome is all-cause mortality at 60 days after randomization. Site investigators will be reporting patient status at 60 days, irrespective of whether the patient continued hospitalized in the same hospital, in another type of health care facility, or discharged home. If patients are discharged alive from hospital before day 60, the information on clinical status at 60 days will be obtained from the electronic clinical record. The Public Health Care System in Spain provides information about the clinical status of any patient through the electronic clinical record system that exists in any public hospital, city, province, or region. In the few cases in which no information could be not obtained from the electronic clinical record (e.g., the patient is not in contact with the outpatient clinic or home care professionals), the local investigator will contact the patient or relatives by phone to ensure the status of the patient at day 60 after randomization. In addition, lead investigators in each site will confirm the recorded 60-day mortality at the time of data analysis.

The secondary outcome is the number of VFDs at 28 days, defined as the number of days alive and free of MV from the day of randomization (day 1) to day 28 after enrollment, on which a patient breathe without assistance. For a day to be considered a ventilator-free day, the patient must breathe without assistance for the full 24 h, i.e., for every breath during that day. The following considerations will be taken into account when calculating the number of VFDs: (i) successful liberation from MV should last more than 48 h without reintubation in patients who survive 28 days after randomization; (ii) extubation only count from the last successful extubation within a 28-day survivor; and (iii) VFDs are awarded zero days if the patient is ventilated for 28 days or more, or die before 28 days (irrespective of intubation status) [20]. Other clinical outcomes include mortality in the ICU, mortality at day 28, duration of MV, length of stay in the hospital for survivors, and the time (in days) from treatment initiation to death. Virologic measures will include the proportions with viral RNA detection over time. Safety outcomes in both groups will include adverse events that occurred during treatment (hyperglycemia, new infections), serious adverse events, and premature discontinuation of treatment.

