### Reporting adverse events

According to Spanish legislation, adverse events should be reported to the Trial Coordinator and to the referral Ethics Committee for review. All adverse events occurring during the study observed by the investigator will be recorded on the data forms. An adverse event is defined as any untoward medical occurrences in a patient during the trial that are not considered related to the clinical state of the patient. Serious adverse events related to the protocol will be sent to the DSMB within 24 h after being received by the trial coordinator. Expected adverse events or complications related to the protocol would include occurrence of hyperglycemia (blood glucose > 180 mg/dL) and new infections (e.g., pneumonia or sepsis) after randomization. All unexpected, and related or possibly related, adverse events will be reported to the institutional review board. Adverse events considered related to the trial, as judged by the investigators, will be followed until resolution or until the event is considered stable. Related adverse events that result in a participant’s withdrawal from the study or are present at the end of the study will be followed up until a satisfactory resolution occurs. The investigator would seek information on adverse events by specific questioning and examination.

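### Hyperglycaemia is compared between open-label arms on sparse, ICU-conditioned CRF days plus investigator-observed events, which leaves room for detection bias of unknown size

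*Protocol article*

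**What the plan says.** Under Outcome measures, the safety outcomes for both groups include "adverse events that occurred during treatment (hyperglycemia, new infections), serious adverse events, and premature discontinuation of treatment". Reporting adverse events supplies the threshold: expected events include "occurrence of hyperglycemia (blood glucose > 180 mg/dL) and new infections" after randomisation.

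Clinical and laboratory monitoring fixes the scheduled capture: the CRF "captures data on lung mechanics, gas-exchange, and routine biochemistry and hematological test on days 0", 1, 3, 6 and 10, then every 10 days, together with the last day of mechanical ventilation, with the condition that the patient is still in the ICU. The legend to Fig. 2 carries a similar ICU condition for asterisked items, but the figure is not available here. The same sentence opens by saying that patients are assessed daily with the CRF. The named tests are: "Recommended lab determinations include creatine phosphokinase (CPK), D-dimer, ferritin, lactate dehydrogenase (LDH), troponin, lactate, creatinine, procalcitonin, C-reactive protein (CRP), lymphocyte count, and interleukin-6 (IL-6". That is eleven tests, and glucose is not one of them.

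Dosing runs for up to 10 days, "independently of the intubation status" (Dexamethasone therapy and general procedures).

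Outside the scheduled days, Reporting adverse events has the data forms record the adverse events that the investigator observes. It defines an adverse event as one not considered related to the patient's clinical state. The Discussion names the lack of blinding and of a placebo as a major limitation.

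**The concern.** Whether a patient has at least one value above 180 mg/dL depends on how many values are looked at and on who decides that a value is an event. No passage sets a glucose frequency common to both arms, and monitoring follows standard care. Three steps can therefore differ by arm in an open-label trial:

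- **Checking.** Staff who know that a patient is on a corticosteroid may measure glucose more often.
- **Recording.** Scheduled laboratory capture depends on ICU stay, while dosing may continue after the patient leaves. If one arm leaves the ICU sooner, its scheduled capture stops sooner.
- **Attribution.** The same reading of 190 mg/dL can be put down to critical illness in a control patient and left out, and put down to the drug in a treated patient and recorded.

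At stake is the reported size of a named harm of the study drug. The primary outcome (60-day mortality) and ventilator-free days are not affected.

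**Working it through.** The article gives no numerical figure for this outcome, so there is none to reproduce. The check is a count from the schedule, followed by an illustration whose inputs are assumptions.

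**1. Scheduled coverage.** The CRF laboratory days are 0, 1, 3, 6 and 10 (Clinical and laboratory monitoring). The possible dosing days are 1 to 10 (Dexamethasone therapy and general procedures). The overlap is days 1, 3, 6 and 10, so 4 of 10. It becomes 5 of 10 if the last ventilated day falls on another dosing day. Two of the four, days 1 and 3, fall in days 1 to 5.

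**2. Equal capture.** Let q be the chance that a given day shows a value above 180 mg/dL, and k the number of days seen. With independent days, P(at least one) = 1 − (1 − q)^k. If q and k are the same in both arms, the difference is zero by construction. If the drug has a real effect, say q = 0.10 in controls and 0.20 in treated patients, the difference still shows:
- k = 4: (1 − 0.8^4) − (1 − 0.9^4) = 0.590 − 0.344, about 25 points.
- k = 10: (1 − 0.8^10) − (1 − 0.9^10) = 0.893 − 0.651, about 24 points.

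Sparse but equal capture lowers the recorded rates (34% instead of 65% at q = 0.10). It creates no false difference.

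**3. Unequal capture, assumed extreme.** Suppose there is no true effect, and one arm is seen on 4 days and the other on all 10. To allow for patients who run persistently high, q is also given a beta distribution across patients with mean q and correlation ρ. Then a = q(1 − ρ)/ρ, b = (1 − q)(1 − ρ)/ρ, and P(none in k) is the product of (b + i)/(a + b + i) for i = 0 to k − 1. For example, with q = 0.10 and ρ = 0.3, a = 0.233 and b = 2.1, which gives 24.3% over 4 days and 35.9% over 10.

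| q | 4 days, independent | 10 days, independent | Difference, independent (points) | Difference, ρ = 0.3 | Difference, ρ = 0.6 |
|---|---|---|---|---|---|
| 0.05 | 18.5% | 40.1% | 21.6 | 7.0 | 2.7 |
| 0.10 | 34.4% | 65.1% | 30.7 | 11.7 | 4.8 |
| 0.20 | 59.0% | 89.3% | 30.2 | 16.1 | 7.6 |
| 0.40 | 87.0% | 99.4% | 12.4 | 14.1 | 9.1 |

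Differences are taken before rounding. For q from 0.05 to 0.20, independent days give 22 to 31 points. With ρ of 0.3 to 0.6 the range is 3 to 16 points, and adding q = 0.40 does not widen it. At q = 0.40 the independent difference falls to 12 points because nearly every patient is positive in either arm.

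**4. A smaller imbalance.** If the arms differ by one day (4 against 5, independent days), the false difference is q(1 − q)^4: 4 points at q = 0.05, 7 at 0.10 and 8 at 0.20.

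The values of q, k by arm and ρ are not in the documents. These figures show how the mechanism behaves and do not estimate the bias.

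**The case against.** The case on the other side is substantial.

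- The CRF schedule applies regardless of arm. A reader might infer from 4 days in 10 that the comparison mostly reflects how often glucose was checked, or cannot be interpreted. The documents do not support this. Equal sparse capture leaves a true difference visible, and no passage says that checking does differ by arm.
- Glucose is not shown to be uncaptured. Routine biochemistry is recorded, the test list is only recommended and is worded as open, and the CRF itself is not shown. The daily-assessment wording also makes the schedule sentence ambiguous. All that can be said is that glucose is not named.
- Adverse-event recording is a second route, with active enquiry, and is tied neither to the laboratory days nor to the ICU. This stands, so the scheduled days are not the only source. But it is also the route most exposed to knowledge of the arm, because it depends on what the investigator observes and attributes. Questioning and examination do not amount to a glucose-sampling rule.
- A reader might infer that patients already above 180 mg/dL before randomisation count as events. The text speaks of occurrence after randomisation, so this does not follow.
- ICU exit within 10 days may be uncommon, since the Background describes weeks of ventilation. A patient who leaves on day 7 loses only the day-10 laboratory point. This limits the ICU condition to a minor contribution.

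**Conclusion.** The point holds in a limited form. Hyperglycaemia is a compared safety outcome with a stated threshold, but the article fixes no common ascertainment of glucose across days 1 to 10. Scheduled biochemistry reaches 4 of those days (5 with the last ventilated day) and is conditioned on ICU stay. The rest depends on observation and attribution by investigators who know the arm. The comparison is therefore open to detection bias of unknown size.

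The only sizes available are illustrative: 22 to 31 points with independent days and 3 to 16 points with within-patient correlation of 0.3 to 0.6. Both assume no true effect and the extreme of 4 days seen in one arm against 10 in the other. Partial imbalance gives less, and equal capture gives none. This is a cheap improvement to a safety outcome and does not challenge the trial's main comparison.

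**What to change.** For both arms, on each study day 1 to 10 while the patient is in hospital, whether in the ICU or on the ward, transcribe two items from the chart: the highest blood glucose and the number of glucose measurements. Define the outcome as at least one value above 180 mg/dL on days 1 to 10, regardless of attribution. Report it by arm alongside day-0 status and the number of measurements per patient. Recording insulin use is optional.

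The number of measurements is essential, because a daily maximum still rises with more readings. Reporting the number by arm does not remove unequal checking, but it shows the reader whether it occurred. The fixed window also gives the control arm, which receives no study drug, the same observation period.

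The cost is data entry of at most 2 × 10 = 20 values per patient, or 20 × 200 = 4,000 values for the trial. No extra tests are needed and patient management does not change. Values that are not captured cannot be restored at the analysis stage, so the change belongs in the CRF now.
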